#### Primary outcomes

The primary outcome measures will be general cognitive function (MoCA [35], MMSE [36]).

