#### Diagnosis criteria

MCI will be diagnosed using Petersen diagnostic criteria as follows [39]: 1) Chief complaint: memory decline; 2) MoCA score of 13–14 for illiteracy, 19–20 for patients with primary school education(1–6 years education), 24–25 for those with junior high school education(≥ 7 years education) [40]; 3) An MMSE score of 24–30 indicates the absence of dementia [41]. (4) ADL will be used to measure the intact activities of daily living (Lawton–Brody ADL score < 18) [38].

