### Sample size calculation

The required sample size is estimated using PASS v11.0 (NCSS, Kaysville, UT, USA) based on a completely random design for comparing the means of two independent samples. To our knowledge, there is no previous study on a stratified support pattern-based internet-assisted self-management therapy for DM-MCI in mainland China, so we estimate the effect size of one of the outcomes (HbA1c) based on previous research on patients with DM-MCI [42]. This study find that HbA1c scores in intervention and control group are 6.49 ± 1.59 and 6.97 ± 0.73, respectively. A sample size of 34 participants per group was determined to be sufficient to detect an effect with a type 1 error rate of 5% (α = 0.05) and 90% power (β = 0.1). A total of 68 participants will be needed, with 34 participants per group. Considering a 20% loss of follow-up rate, the final sample size is 86, with 43 participants per group.

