### Intervention

#### Intervention group

In this study, the intervention group will adopt a SISMT. After the completion of the baseline survey, participants will formulate personalized intervention measures and optimize and expand their knowledge through hierarchical strategies to improve their self-management behavior. Based on our previous research in this study, the patients will be divided into four categories according to cognitive function and self-management ability: (1) high cognitive high management, (2) high cognitive low management, (3) low cognitive high management, and (4) low cognitive low management. Four WeChat groups will be formed to intervene separately to prevent communications between each category of participants in the intervention group. Self-management interventions targeted to patients with DM-MCI will be implemented, including diet, exercise, drug intake, psychology, and cognition. To achieve stratified intervention with different intensity, the content will remain the same for each group, but the frequency will differ. The intervention plan is shown in Table 1. All intervention content will be implemented through home self-monitoring and WeChat feedback. When patients experience suboptimal blood sugar monitoring, researchers will guide them in regulating self-management behavior. If behavioral regulation is ineffective, contact the attending physician for medication guidance. The outcome indicators will be collected at three time points: baseline, 12 and 24 weeks, respectively.

**Table 1 Tab1:** Intervention plan of the the stratified support pattern-based internet-assisted self-management therapy for DM-MCI

Patient type	Intervention method	Specific content

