### Outcomes

#### Outcome measures timeline

To compare the outcomes of the self-management interventions provided under the SISMT and HMI, a baseline (W0) survey will be administered to both the experimental and control groups before the start of each pattern. Outcome indicators will be collected 12 weeks (T1) and 24 weeks (T2) after the intervention to compare the effects of the two patterns (Table 2). The indicators will be assessed by experienced staff members who will be blinded to the group allocation. Outcome indicators and measurement tools are as follows (Domains /characteristics of tools see Table 3):

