### Statistical analysis

All data analysis will be performed using SPSS Statistics v21.0 (IBM). To ensure that they are blinded to group assignment, the outcome assessors and data analysts will not interact with the participants except during data collection (in the case of outcome assessors). Demographic and other baseline characteristics will be summarized using descriptive statistics. If necessary, the results will be adjusted for potential confounders, such as age, gender, and education. Quantitative data will be expressed as frequencies or rates and statistical analysis will be carried out using the *χ*^2^ test. If these data are normally distributed, they will be expressed as (*x* ± *s*). The effects of the interventions (between-group differences) will be calculated with linear mixed models using interaction terms (group allocation versus time), which are equivalent to the between-group differences. The within-group differences will be calculated using repeated measures ANOVA. *P*-values < 0.05 will be considered statistically significant. The data will be reviewed before analysis. The Statistical Package for the Social Sciences (SPSS) software will be used for all analyses. The clinical relevance of the results will be confirmed by calculating the effect size (Cohen d) of the significant differences found between the assessments. The following effects will be considered: small: 0.00–0.49; medium: 0.50–0.79; high ≥0.80 (Cohen, 1988). Comparison between the four subgroups within the intervention group using ANOVA test.

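### MoCA and MMSE are both primary with no rule for which must succeed, so the 5% type 1 error is not assured; the primary time point is also worded two ways

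*Protocol article*

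**What the plan says.** **Primary outcomes.** The Primary outcomes section reads: "The primary outcome measures will be general cognitive function (MoCA [35], MMSE [36". It gives no order, no composite and no statement on whether one or both must show a benefit.

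**Hypothesis.** The Study objectives and hypotheses section expects greater improvement in cognitive function scores (plural, no scale named) in the SISMT arm 12 weeks after the intervention. It calls this the first primary hypothesis, but no second one follows.

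**Criterion.** The Sample size calculation section states a "type 1 error rate of 5% (α = 0.05) and 90% power (β = 0.1"). These figures are for HbA1c, a secondary outcome. The Statistical analysis section says that P-values below "0.05 will be considered statistically significant". It estimates effects through group-by-time terms of a linear mixed model and does not single out one contrast as primary.

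**Timing.** The Background gives the intervention a length of 12 weeks. The Intervention group section says: "The outcome indicators will be collected at three time points: baseline, 12 and 24 weeks, respectively". The Control group section agrees. The Outcome measures timeline section says: "Outcome indicators will be collected 12 weeks (T1) and 24 weeks (T2) after the intervention". The Trial design section attaches a post-intervention label to the 24-week visit.

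**The concern.** A primary analysis should leave no doubt about which result makes the trial positive. Here two scales share primary status and each can be tested at 0.05. If the analyst may point to whichever scale reaches significance, the trial has two chances to succeed by luck, and its overall error rate is no longer the 5% used in planning. If both must succeed, the error rate is safe but the power is that of a joint requirement. The text supports either reading.

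The timing matters for a different reason. An effect at the end of a 12-week programme and an effect 12 weeks after it has stopped are different questions, immediate against sustained benefit. The wording should settle which one is primary before anyone sees data.

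**Working it through.** **Inputs from the protocol article**
- Number of primary scales: 2 (Primary outcomes).
- Threshold: 0.05 (Statistical analysis). The sample size section does not state sidedness; I take two-sided.
- Intervention length: 12 weeks (Background).

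**Assumed input**
- Correlation ρ between the MoCA and MMSE test statistics. It is not given, so I use 0 to 0.9.

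**Step 1: the plan's own figure.** One test at 0.05 has a type 1 error of 5%. That holds if a single scale at a single time decides the trial.

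**Step 2: either scale suffices.** With no true effect on either scale:

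P(at least one significant) = 0.05 + 0.05 − P(both significant)

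If the tests are independent, this is 1 − 0.95² = 0.10 − 0.0025 = 9.75%. For correlated tests, P(both significant) comes from the bivariate normal distribution with cut-offs at ±1.96.

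| ρ | Both significant | Either, each at 0.05 | Either, each at 0.025 |
|---|---|---|---|
| 0 | 0.25% | 9.75% | 4.94% |
| 0.3 | 0.49% | 9.51% | 4.84% |
| 0.5 | 0.93% | 9.08% | 4.65% |
| 0.7 | 1.66% | 8.35% | 4.30% |
| 0.8 | 2.19% | 7.81% | 4.02% |
| 0.9 | 2.97% | 7.04% | 3.62% |

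A simulation with two million draws agrees to within about 0.02 percentage points (for example 7.05% at ρ = 0.9).

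**Step 3: both scales required.** With no effect on either scale, the error is the second column, 0.25% to about 3.0%. If one scale truly responds and the other does not, the error rises towards 5% but cannot pass it. The cost is power: the joint power cannot exceed the smaller of the two single-scale powers. I give no figure, because the article states no power for either scale; its 90% belongs to HbA1c.

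**Step 4: what T1 means.**
- Counted from the start of the intervention: T1 = week 12, T2 = week 24.
- Counted from its end: T1 = 12 + 12 = week 24, T2 = 12 + 24 = week 36.

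Week 24 is thus T2 on one reading and T1 on the other. The Intervention group and Control group sections fit the first. The hypotheses and the Outcome measures timeline can be read as the second.

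**The case against.** **The analysis plan may settle it.** The article is condensed, and multiplicity is often handled in a SAP that is not shown. The 0.05 line can also be read as a general significance convention rather than a rule for trial success. This has some force, and it is why the conclusion is that 5% is not assured rather than that it is lost. But the article itself fixes the primary outcomes, the hypothesis and the threshold, and together they do not define a success criterion. What makes the trial positive is a protocol-level choice.

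**The time may already be clear.** The hypothesis names one time, 12 weeks, and several sections list 12 and 24 weeks alongside baseline. Table 2, the schedule, is not shown and may resolve it. The narrative sections still need to agree with it.

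**Stronger readings that a reader might infer, and why they fail**
- *The 5% level definitely fails.* It does so only under an either-scale rule, which the article does not state.
- *Two scales and two visits make four chances to win.* The hypothesis names one time, and nothing lets the later visit carry it. The loose wording is about which calendar week T1 is. It adds error only if the week is chosen after seeing data or if both visits count.
- *The MMSE entry limit inflates error.* The Diagnosis criteria say: "An MMSE score of 24–30 indicates the absence of dementia". With a maximum of 30 (Table 3), this leaves 0 to 6 points of headroom. Under randomisation a ceiling affects sensitivity, not type 1 error: a null simulation with MMSE restricted to 24–30 and capped at 30 (assumed mean 27, SD 2, SD of change 1.5, 34 per group) gave 4.99%. MoCA is limited at entry too, to two-point bands by education (13–14, 19–20, 24–25), which leave 16–17, 10–11 and 5–6 points below 30. A between-group difference could also come from less decline, an aim named in the Abstract. Headroom is at most a sensitivity argument for preferring MoCA.

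**Conclusion.** The concern holds in this form: with two primary scales, one threshold and no success rule, the stated 5% type 1 error is not assured. Under an either-scale rule it is about 7% to 9.75%, resting on an assumed correlation of 0.9 to 0 and two-sided tests. Under a both-scales rule it is at or below 5%, with a loss of power that the article gives no basis to quantify.

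Separately, the primary time is ambiguous between end of treatment and 12 weeks later. That leaves the primary question undefined, but does not by itself raise the error rate.

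**What to change.** Before unblinding, name one primary endpoint. One suitable choice is the SISMT minus HMI difference in MoCA at week 12 from randomisation, tested at two-sided 0.05 as that single group-by-time contrast of the mixed model, with MMSE and all week-24 results secondary. If both scales are to stay primary with either able to succeed, use Holm or 0.025 each; the last column of the table shows that 0.025 each keeps the error at or below 5%. Requiring both also controls error, if the sponsor accepts the lower power and says so.

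Give T1 and T2 in weeks from randomisation in every section and in the schedule table.

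No extra patients or visits are needed for the single-endpoint option. MMSE loses primary status, or some power is lost under a split, and the registered outcome must be updated. Screening is already under way, so the change should be dated and made without sight of outcome data by arm.

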#### Secondary outcomes

The secondary outcome measures will include several commonly used measures of specific domains of cognitive function, psychological indicators, blood glucose control (FBS, HbA1c, PBS) and other relevant indicators. The measures of specific domains of cognitive function (memory, language, attentions) will comprise the Auditory Verbal Learning Test (AVLT) [43], Symbol Digital Modalities Test (SDMT) [44]. Psychological status will serve as the secondary index of this study. This will include anxiety, depression, well-being, quality of life, self-efficacy, and self-esteem. The Self-Rating Anxiety Scale (SAS) will be used to measure anxiety [45] and the Geriatric Depression Scale (GDS) will measure depression [46]. Well-being will be assessed using the Memorial University of Newfoundland Scale of Happiness (MUNSH) [47]. Quality of Life-Alzheimer’s Disease (QoL-AD) will be used to assess patient quality of life [48], the General Self-efficacy Scale (GSES) will be used to measure self-efficacy [49], and the Self-Esteem Scale (SES) will be used to measure self-esteem [50]. Other relevant indicators include the healthy literacy and self-management behavior which can be used to investigate the patient’s acceptance of the intervention content. Health literacy and self-management behavior will be determined using the Health Literacy Scale for type 2 diabetes and the diabetes self-care scale (DSCS).

### Data collection

FBS, HbA1c, and PBS will be measured and collected from participants' self-reported data. Other data that need to be measured using a scale will be invited participants to the hospital again for measurement and collection.

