**Methods:**

Eighty-four DM-MCI patients will be randomly divided into an intervention group and a control group in a 1:1 ratio. The intervention group will receive a self-management intervention using the stratified support pattern-based internet-assisted therapy (SISMT), while the control group will receive the health manual intervention (HMI). The study recruiter will be blinded to the group allocation and unable to foresee which group the next participant will be assigned to. At the same time, the allocation will be also hidden from the research evaluators and participants. After 12 weeks and 24 weeks, cognitive function, blood glucose, self-management ability, psychological status, health literacy, and self-management behavior of patients in both groups will be measured and compared.

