### Randomization, blinding, and concealed allocation

Ensuring allocation concealment, participants will be randomized (after obtaining written informed consent, eligibility screening, and baseline assessment) to the intervention and control groups at a 1:1 ratio by a study staff member (who will not be involved in participant recruitment or outcome assessment) using Research Randomizer software (http://www.randomizer.org/). Participants in the intervention group will be assigned to different categories of the intervention group based on their cognitive function and self-management characteristics and will receive Intervention measures with different frequencies. Participants in the control group will be assigned to different categories of the control group based on their cognitive function and self-management characteristics, too, but there is no difference in intervention frequency. The participants will then be told their group assignment by the intervention staff. Due to the nature of non-pharmacological interventions, only the outcome assessors and data analysts (not the participants or intervention staff) will be blinded to group allocation.

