High cognition, high management	1. Monitor fasting blood glucose or 2 h postprandial blood glucose 2–3 times a week and provide once a week reminders 2. Learn disease and health-related information and assess diet, exercise, medication, cognitive training, and mental health, once a week 3. Exercise 3 days a week for 20-–40 min each time and provide once a week reminders	**Dietary management:** Mediterranean cuisine, with Omega-3 as the core; Use more fruits and vegetables, fish, olive oil, nuts, beans, and coarse grains. Peanut oil, soybean oil, walnut oil and rapeseed oil can be selected as oil; Fish: Both marine and non marine fish are acceptable; It is not recommended to supplement Vitamins B, E, and complex vitamins to delay cognitive impairment. Recommend low GI foods to control or reduce weight **Exercise management:** 150 min of light to moderate aerobic exercise per week **Medication management:** Medication time, medication method, and medication contraindication **Blood glucose monitoring:** Oral hypoglycemic drugs are used to monitor fasting blood glucose or 2-h postprandial blood glucose 2–4 times a week. If blood glucose control is stable, the interval can be flexibly adjusted, and blood glucose measurement methods (Preprandial blood glucose, pre—post blood glucose matching) can be selected based on one's own blood glucose situation. Those who do not meet the standard for glycated hemoglobin should be tested every 3 months, and once every 6 months after reaching the standard **Cognitive guidance:** Knowledge of cognitive impairment diseases, prevention methods, influencing factors and so on. And appropriate reminders as cognitive stimulation. Cognitive monitoring is followed up every 12 weeks
High cognition, low management	1. Monitor fasting blood glucose or 2 h postprandial blood glucose 3 × a week and provide once a week reminders 2. Learn disease and health related knowledge and assess diet, exercise, medication, cognitive training, and mental health, twice a week 3. Exercise 3 days a week for 20–40 min and provide once a week reminders	
Low cognition, high management	1. Monitor fasting blood glucose or 2 h postprandial blood glucose 3 × a week and provide twice a week reminders 2. Learn disease and health-related knowledge and assess diet, exercise, medication, cognitive training, and mental health 3 × a week	

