#### Wechat operation

WeChat is the intervention medium for this study. The researchers will establish WeChat groups and created WeChat official account before the intervention. The researcher will send the completed content of the WeChat official account to the participants on the WeChat social platform. Participants can use the chat box function of the WeChat social platform to provide feedback and exchange on content of the WeChat official account, and can also interact with other participants in the WeChat group to share their self-management experience and personal insights on health knowledge. And they are required to use this application to inform researchers of their fasting blood glucose level, postprandial blood glucose level, hypoglycemia, diet and exercise status (Fig. 3).

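### Glycaemic outcomes are self-reported by participants who know their arm, and a glucose monitoring and reporting routine is described only for the intervention arm, so the comparison is open to differential bias

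*Protocol article*

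**What the plan says.** **Source of the data.** In the Data collection section, "FBS, HbA1c, and PBS will be measured and collected from participants' self-reported data". The next sentence gives the remaining outcomes a different route: "Other data that need to be measured using a scale will be invited participants to the hospital again for measurement and collection".

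**Who knows the allocation.** The section on randomization, blinding and concealed allocation says "The participants will then be told their group assignment by the intervention staff" and that "only the outcome assessors and data analysts (not the participants or intervention staff) will be blinded to group allocation". The Methods paragraph of the abstract says instead that "the allocation will be also hidden from the research evaluators and participants".

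**Intervention arm.** The Intervention group section and Table 1 describe home glucose checks two to three times a week, depending on the patient category, with weekly or more frequent reminders. Researchers give guidance when monitoring results are unsatisfactory. Under Wechat operation, "they are required to use this application to inform researchers of their fasting blood glucose level, postprandial blood glucose level", along with hypoglycaemia, diet and exercise.

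**Control arm.** The Control group section describes health education after the clinic visit, and a manual on cognitive impairment that is explained to each participant. Outcomes are collected at the same three time points. No glucose monitoring or reporting routine is described.

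**Safeguards stated.** Outcome measures timeline: "The indicators will be assessed by experienced staff members who will be blinded to the group allocation". Limitations: a possible tendency of intervention participants to respond more positively is acknowledged, but for the self-reported questionnaire only.

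**The concern.** HbA1c and fasting glucose can be measured objectively, and such a measurement does not depend on what the participant knows or remembers. The plan gives up that advantage by making the participant the source. The participants are older adults with mild cognitive impairment, they know which programme they are in, and in one arm they report fasting and postprandial glucose to the same team that coaches them on it.

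Better glucose control (FBS, HbA1c, PBS) is the first secondary hypothesis listed, and HbA1c is the outcome on which the sample size was based. A between-arm difference in these measures could reflect how values were obtained and reported as well as how well glucose was controlled, and the analysis could not separate the two.

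**Working it through.** The plan gives no figure for this point, so the check sets its statements side by side.

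**1. Is self-report really the source?** Yes. The Data collection section names it for all three glycaemic measures and contrasts it with the hospital visit used for the scales. The word for measuring in the same sentence leaves open that a participant passes on a laboratory or meter result, but what reaches the trial is still the participant's report.

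**2. Do participants know their arm?** Yes, on the detailed text. The randomization section says they are told and gives the reason (a non-pharmacological intervention). The Trial design section calls the study single-blind, and the Study aim section names only the assessor as blinded; both fit that reading. The abstract contradicts it.

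**3. Do the arms differ in how values arise?**

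| Element | Intervention arm | Control arm |
|---|---|---|
| Outcome time points | Baseline, 12 and 24 weeks | Same |
| Home glucose checks | 2–3 times a week | None described |
| Reminders to measure | 1–3 times a week, by category | None described |
| Required reporting of FBS and PBS | Yes, by WeChat | None described |
| Required WeChat reporting of HbA1c | Not listed | None described |
| Researcher response to the values | Yes | None described |

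For FBS and PBS the described number of readings, prompts and reporting channel differ by arm. For HbA1c they do not differ through WeChat; its exposure rests on self-report and knowledge of the arm.

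**4. Does assessor blinding close the gap?** No. A blinded staff member who writes down a number supplied by an unblinded participant records whatever error that number carries.

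**5. Which way would the error go?** Not known. Participants who are coached on their glucose may report the more favourable readings, which would favour the intervention. More frequent checks may also catch high values that control participants never see, which would work against it. The document supports neither direction and gives nothing from which to estimate a size.

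**The case against.** **The evidence is for exposure to bias, not for bias.** This stands. A self-reported HbA1c may be a faithfully relayed laboratory value, and then the error would be small. The text does not show that the comparison is biased, only that the stated source leaves it open to bias.

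**The WeChat log is never named as the outcome dataset, and its reporting rule does not list HbA1c.** This also stands. The asymmetry in routine applies to FBS and PBS, and only if outcome reports are shaped by that routine.

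**Table 1 might seem to leave gaps in HbA1c.** It says "Those who do not meet the standard for glycated hemoglobin should be tested every 3 months, and once every 6 months after reaching the standard". A reader might infer that many participants would have no new HbA1c at 12 weeks, and that missingness would depend on the outcome itself. The document does not support this. The line is part of the self-care content of the intervention plan, outcome collection is fixed at baseline, 12 and 24 weeks in both arms, and the share of participants at the standard is not given.

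**A magnitude could be put on it.** One could assume a reporting error and express it as a share of the 0.48-point HbA1c difference (6.97 − 6.49) behind the sample size. That would only restate the assumption, so no such figure is offered.

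**These are secondary outcomes, and an article may leave measurement logistics to the full protocol.** The first part is right and limits the weight of the point: MoCA and MMSE are collected at the hospital by blinded staff. The second part does not answer it, because the criticism is of a data source that the article states, not of a detail it omits.

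**Conclusion.** The point holds as an avoidable weakness in the secondary glycaemic comparison. All three measures are self-reported by participants who know their arm, and for FBS and PBS a monitoring and reporting routine is described in one arm only. The resulting bias is of unknown size and direction. Neither assessor blinding nor the Limitations section deals with it.

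The conclusion assumes that the Data collection sentence means what it says, and that the detailed blinding text, not the abstract, describes the trial. If allocation really were hidden from participants, the reporting part of the concern would weaken, but the difference in described monitoring would remain. The primary cognitive comparison is not touched. Whether the sample size on HbA1c is correct is a separate matter and is not needed here.

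**What to change.** - **HbA1c and fasting glucose:** in both arms, take the values at T0, T1 and T2 from hospital laboratory results, either by record look-up or from a routine sample at the hospital visit already made for the scales. Apply one window around each time point, the same in both arms.
- **PBS:** define it as the same number of readings in the same window in both arms.
- **Home readings:** state that glucose values collected in the intervention arm through WeChat are process data and are not used as outcomes.
- **Blinding:** reconcile the abstract with the randomization section, so that only outcome assessors and data analysts are described as blinded.
- **Limitations:** if any glycaemic measure stays self-reported, extend the acknowledged reporting bias to it.

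**Cost.** The hospital visits are already planned, and the hospital record system is already used to confirm the diabetes diagnosis. The added burden is a routine laboratory test for participants without a result in the window, and a set of readings for PBS in the control arm. Correcting the abstract costs nothing.

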#### Inclusion criteria

1) Meet the diagnostic criteria for diabetes (The diagnosis of diabetes is based on the doctor's diagnosis results in the hospital diagnosis and treatment system). 2) Meet the diagnostic criteria for mild cognitive impairment. 3) ≥ 60 years of age. 4) No obvious visual or hearing impairments. 5) Participants have good communication skills and can cooperate with researchers to complete the survey questionnaire. 6) Able to use Internet device dependently.

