### Limitations

This study has some limitations. First, the design does not allow blinding of the intervention implementer. Second, the effect of a long-term intervention will remain unknown following study completion. Third, there may be a selection bias in the participant pool given the requirement for patients to use smartphones independently. In addition, since participants in the intervention group may tend to provide a more positive response, the self-reported questionnaire may introduce a potential bias and affect the accuracy of the trial to some extent.

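### The three secondary glucose outcomes come from participants' self-report, so the stated blinded assessment does not cover them, and reporting may differ by arm

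*Protocol article*

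**What the plan says.** The Data collection section gives one source for all three glucose measures. Its sentence begins "FBS, HbA1c, and PBS will be measured and collected from participants" and names self-report as that source; in full it reads: "FBS, HbA1c, and PBS will be measured and collected from participants' self-reported data". It then treats everything else differently: "Other data that need to be measured using a scale will be invited participants to the hospital again for measurement and collection". The hospital visit is thus described for the scales and not for glucose.

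Outcome measures timeline makes a general statement about who assesses outcomes: "The indicators will be assessed by experienced staff members who will be blinded to the group allocation". It makes no exception for glucose, and the Secondary outcomes section lists FBS, HbA1c and PBS among the outcomes.

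On knowledge of allocation, the randomization section says: "The participants will then be told their group assignment by the intervention staff". It adds that only outcome assessors and analysts are blinded. The Abstract's Methods paragraph says instead that allocation is hidden from participants as well as evaluators.

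The Limitations section accepts that "participants in the intervention group may tend to provide a more positive response", but ties this to the self-reported questionnaire and does not mention glucose.

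**The concern.** A blinded staff member who receives a number from a participant records it but does not assess it. If the participant knows the arm, the value is open to influence from that knowledge, whoever writes it down. The blinding statement then promises more than the data collection method delivers.

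The two arms also have different reporting environments. Under Intervention group and Wechat operation, SISMT participants monitor at home, must send fasting and postprandial values to the researchers, and receive guidance when readings are suboptimal. The Control group section describes a health manual and an explanation of it, with no glucose reporting channel. SISMT participants therefore have an audience for their readings and controls do not. That is a plausible route to arm-dependent reporting, by selection of favourable readings or by differences in completeness.

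At stake is the first secondary hypothesis, better blood glucose control under SISMT. HbA1c is also the outcome on which the sample size is based. A difference at 12 or 24 weeks could not be cleanly separated from a difference in reporting.

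**Working it through.** The point rests on comparing the text. The arithmetic only illustrates a possible consequence.

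**Text, side by side**

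1. Source of FBS, HbA1c and PBS: self-report (Data collection).
2. Assessor of the indicators: blinded staff, no exception (Outcome measures timeline).
3. Status of the reporter: told the arm (randomization section). The Abstract disagrees. The randomization section is the more specific text and explains that blinding participants is not feasible with this kind of intervention. The Limitations section also expects answers that depend on arm. I therefore take participants as unblinded.
4. Items 1 and 3 together mean that an unblinded person supplies the value. Item 2 cannot then be true of these outcomes in the sense that matters for bias.
5. Randomization follows baseline assessment, so T0 reports precede knowledge of the arm, while T1 and T2 reports follow it. A shift in reporting would appear as a group-by-time difference, which is the effect the Statistical analysis section plans to test.

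**Illustration of size**

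Inputs from Sample size calculation: HbA1c 6.49 ± 1.59 and 6.97 ± 0.73, with 34 per arm before allowance for loss. I use 34 as stated; whether it follows from those inputs is a separate question. The protocol gives no figure for reporting bias, so the shift b is my assumption, set at 0.1, 0.2 and 0.3 towards lower values in SISMT, with no true difference.

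- Planned difference: 6.97 − 6.49 = 0.48.
- Pooled SD: √((1.59² + 0.73²)/2) = 1.237.
- Standard error of the difference: 1.237 × √(2/34) = 0.300.
- Two-sided rejection probability (normal approximation): 1 − Φ(1.96 − b/SE) + Φ(−1.96 − b/SE).

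| Assumed shift b | Share of 0.48 | b/SE | Rejection rate, normal | Rejection rate, noncentral t |
|---|---|---|---|---|
| 0.1 | 21% | 0.33 | 6.3% | 6.2% |
| 0.2 | 42% | 0.67 | 10.2% | 10.1% |
| 0.3 | 63% | 1.00 | 17.0% | 16.6% |

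This is a two-sample comparison at one time point. The planned analysis is a linear mixed model with a group-by-time term. Its standard error depends on a within-person correlation that the protocol does not give, so the inflation there could be smaller or larger.

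**The case against.** **Self-report need not mean recall.** The wording is loose, and participants may be relaying a meter reading or a printed result. HbA1c cannot be read from a home glucose meter, so a laboratory value presumably lies behind it. This stands: the protocol does not say that values come from memory. But a value relayed by someone who knows the arm, with no check against a source, is still neither blinded nor verified.

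**The blinding sentence may be meant for the scales.** It leads into the list of measurement tools, and Table 3 contains only scales. That reading is possible and would reduce the conflict to a missing exception. Because glucose is listed as an outcome, the exception still has to be written.

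**Memory impairment.** A reader might infer that cognitive impairment itself biases the results, since the diagnosis includes "Chief complaint: memory decline". The documents do not support that. Eligibility also requires an MMSE of 24–30, intact daily living and good communication, and inability to use a smartphone independently is an exclusion. Poor memory alone would add noise in both arms rather than a difference between them. The concern rests on knowledge of allocation and unequal reporting channels.

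**Source results may not exist.** The hospital system is cited only for diagnosis: "The diagnosis of diabetes is based on the doctor's diagnosis results in the hospital diagnosis and treatment system". Nothing shows that it holds dated HbA1c or FBS results at T0, T1 and T2. Only most participants come from the named clinic, Table 1 allows longer gaps between HbA1c tests once the standard is reached, and no section says controls have meters. This objection stands and limits what the fix can demand.

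**Conclusion.** The point holds for three secondary outcomes. As written, FBS, HbA1c and PBS are self-reported by participants who are told their arm, so the general claim of blinded assessment does not apply to them. The reporting channel is described for one arm only, and the Limitations section acknowledges the bias only for questionnaires.

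A reader might go further and say that the trial has lost its only objective outcomes. That is not so. MoCA and MMSE (primary) and AVLT and SDMT (secondary) are performance tests administered by staff, and this point does not touch them.

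Nor do the documents show that bias will occur, or how large it would be. The figures of about 6%, 10% and 17% depend entirely on the assumed shift and on a single-time test, and are illustrative only. The conflict in the text does not depend on them. This should be corrected, but it does not threaten the primary comparison.

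**What to change.** 1. In Data collection, name the source document for each glucose outcome, identically for both arms. Take HbA1c and FBS from the dated laboratory report, either in the hospital record or brought by the participant to the visit already planned for the scales. Take FBS or PBS from the stored meter reading where one exists. Have blinded staff transcribe the values.
2. State that values sent through WeChat serve intervention delivery only and are not outcome data.
3. Where no source result exists and self-report is kept, exclude that outcome from the blinding statement in Outcome measures timeline, label it self-reported and unblinded, and extend the Limitations paragraph to it.
4. Reconcile the Abstract with the randomization section on whether participants know their allocation.

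The cost is some transcription work, a few sentences of text, and some values with no source result. No new blood test is required by this change. If the sponsor chose to add one to fill the gaps, that would be an extra procedure with its own burden.
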